#### Implementation

2.1.2

Concurrent with the effectiveness evaluation, we will conduct a mixed-methods study aimed at evaluating delivery of the model and describing contextual factors and barriers to FCU® implementation and sustainability within a regional autism service setting. This work will be informed by the Exploration, Preparation, Implementation, Sustainment (EPIS) framework (34), which focuses on evidence-based practice implementation in publicly funded services, and the FCU® Implementation Framework (35), which emphasizes the inner context and FCU®-specific facilitators and barriers at each EPIS stage (36). Specifically, implementation aims are to:

Evaluate metrics related to the adoption, implementation, and sustainable delivery of the FCU® within the urban outpatient hospital-based Autism Program and characterize implementation facilitators and barriers using a mixed-methods approach.Describe autism therapists’ experience of FCU® training, supervision and delivery, and measure sustained competence and fidelity FCU® model delivery.Describe leadership impressions/experiences of providing the FCU® within the wider Autism Services setting and obtain key administrative metrics related to clinical delivery.Obtain caregiver and youth impressions of participating in the FCU® as provided within an Autism Program setting.Describe the processes and effectiveness of outreach, screening, and referral approaches to inform future implementation efforts.

#### Sample and recruitment

2.1.3

The study sample consists of 80 children/youth with ASD and high levels of EBP and their caregiver(s).

##### Inclusion criteria

2.1.3.1

Child 6–17 years of age.Confirmed diagnosis of ASD.Enrollment in the Ontario Autism Program (OAP).Minimum developmental age of 2 years.Elevated EBP as determined by high or very high scores on the emotional problems (≥ 5), hyperactivity (≥ 8), and/or conduct problems (≥ 4) scales of the Strengths and Difficulties Questionnaire (SDQ) (37) OR a score ≥ 12 on the irritability subscale of the Aberrant Behavior Checklist (ABC) (38).Residing with the same caregiver for at least 5 days/week OR every other week for the past 2 months and the foreseeable future.

##### Exclusion criteria

2.1.3.2

Caregiver with insufficient knowledge of English to complete questionnaires.Current enrollment in another intervention study.Active significant safeguarding concerns (e.g., child with severe acute self-harm or aggression requiring hospitalization; acute caregiver suicidality; and medical fragility).Prior participation in the FCU® in another setting or study.

Recruitment settings include: referrals from family service coordinators who support service navigation within the regional autism program, ASD diagnostic hubs, school boards, community organizations, and healthcare providers. Families may also self-refer or be referred by other research study staff (provided they complete a consent to contact so their information can be shared with research staff).

#### Screening

2.1.4

Interested caregivers will complete a 20–30 min telephone or in-person screening interview with research staff to hear about the study and assess inclusion/exclusion criteria. Families will be asked some basic questions to assess eligibility (e.g., child age, child’s primary residence and caregivers, participation in other studies, child’s language abilities, and child’s developmental age). Child EBP will be assessed as described above.

The FCU® will be provided within the regional Autism service by government-funded clinicians, therefore participating families must be registered with the provincial OAP. Interested families who are unregistered will be connected to service navigation to facilitate this process.

#### Randomization and blinding

2.1.5

Randomization will occur following the baseline visit to reduce risk of differential attrition. Participants will be randomly assigned to one of two conditions (FCU® or Treatment as Usual) using an internet-based randomization service; https://www.randomize.net/. Randomization will be stratified by child chronological age (6–10 and 11–17 years) and by presence/absence of co-occurring intellectual disability. Participants will be informed of their treatment arm status by the Research Coordinator or another research staff member who will not conduct any follow-up measures.

Participants will be informed of their right to withdraw from the study at any time. Furthermore, the lead principal investigator (LPI) may decide to withdraw a participating family from the study, if required, to mitigate undue risk to caregiver, child, research staff, or FCU® clinician.

Study participants will be withdrawn from the study under the following conditions:

If it is determined that the caregiver or child has an acute psychiatric crisis (e.g., psychosis) that will interfere with the ability to participate in the study.If a caregiver is experiencing an extreme crisis (e.g., related to an abusive or violent relationship) that interferes with the ability to participate in the study.If caregiver, child, research staff, or FCU® clinician experience an adverse event that is deemed by the LPI be an unacceptable safety risk.Death of child or participating caregiver.If participant behaviors or circumstances are deemed to unduly compromise the safety of the treating clinician or research staff (e.g., violence or unsafe behaviors toward research staff or clinician; unsafe conditions in home).If the LPI deems it is in the participants’ best interest to discontinue the study treatment.Loss of custodial caregiver status, if consent not obtained from replacing custodial caregiver (e.g., other caregiver, child protection service).

### Intervention: the Family Check-Up®

2.2

The FCU® is a brief “assessment-as-intervention” that engages caregivers in a collaborative process of assessment, reflection, teaching, and goal-setting. The process typically includes three visits (See Figure 1):

**Figure 1 fig1:**
[figure not shown]
Outline of Family Check-Up® Visits.

#### “Get to Know You” interview (45 min)

2.2.1

The FCU® clinician introduces the FCU® and engages caregivers in an initial interview aimed at establishing a clinician-client relationship, building rapport, and gathering information about unique child and family strengths and challenges, past successes, and future goals.

#### Ecological assessment (60 min)

2.2.2

The assessment visit involves questionnaire and observational tasks to assess risk and protective factors across broad domains: family psychosocial context (e.g., SES, supports, caregiver mental health, and partner support), family management (parenting, family warmth and conflict), and child emotional-behavioral well-being, peer relations, and school success. Questionnaires are completed by primary and any additional participating caregivers and children and youth with developmental ages of at least 11 years.

To address the heterogeneity of social-communication, cognitive and language skills across the spectrum of autistic children and youth, observed Family Interaction Tasks (FITs) and their instructions are tailored to the developmental age of the child. Because the aim is to measure caregiver-child interactions as naturalistically as possible, caregivers are instructed to communicate with their child in their typical way and to support their child to complete the tasks or talk with them about a topic.

Caregivers and children developmentally aged 2–5 years engage in a teaching task, engagement in collaborative play, and clean-up. A selection of toys with broad developmental age ranges were chosen to accommodate older youth who may fall within a developmental age of 2–5 years for the purposes of this task. For children aged 6–10 and 11–17 years, tasks are more discussion-based and address child and family strengths, school experience and goals, parental online monitoring, solving a family problem, and planning a fun family activity. Tasks are designed to elicit key domains of parenting behavior shown to be important for emotional and behavioral adjustment across age groups (i.e., relationship-building, positive behavior support, limit-setting and monitoring, and non-reactive parenting). The interactions are videotaped, coded by the clinician according to established FCU® guidelines and incorporated into the feedback with 2–3 clips chosen to highlight child/youth and caregiver strengths and positive interactions, emphasizing examples of effective parenting skills and child/youth response.

Collaborative feedback session (60–90 min): The FCU® clinician provides structured feedback to caregivers based on assessment results using motivational interviewing techniques to engage the caregiver in reflection and “change talk (39)”. The discussion is scaffolded by a visual feedback form that integrates questionnaire, interview and video-based data as well as brief, empirically supported rationales about the interdependencies of child adjustment, parenting, and the family context, tailored to individual child and family profiles. The clinician will also incorporate relevant autism-related child strengths and challenges and a parenting lens, emphasizing evidence-based transdiagnostic positive parenting behavior that support child and youth self-regulation. Strength-based video clips highlighting skillful parenting behaviors and positive parent–child interactions are chosen to optimize caregiver engagement, self-efficacy and motivation. The clinician supports the caregiver to outline goals and collaboratively design a tailored menu of services, with service navigation and advocacy support as needed. Examples of “menu items” may include caregiver engagement in EDP sessions focused on one or more parenting behavior domains collaboratively identified as an area of need, connection to child and youth mental health programs, caregiver support to connect to own mental health services, child recreation programs, housing, or other funding application support.

#### Everyday Parenting (EDP) curriculum

2.2.3

The FCU® clinician and caregiver (s) may decide upon a suite of optional 1:1 EDP sessions, the number and content of which are carefully tailored to parenting strengths, challenges, and goals established during the collaborative FCU® feedback session. The EDP (41) is based on a Social Interaction Learning (41, 42) model of parenting; it supports caregivers to become mindful of interaction patterns with their children (both positive and negative) and to strengthen positive caregiver-child relationships and parenting skills to scaffold child self-regulation. Sessions are provided weekly to biweekly in-person or by Zoom for up to 6 months, an arbitrary cut-off chosen for clinical resource and study timeline purposes, the acceptability of which will be re-evaluated upon study completion.

#### Intervention evidence

2.2.4

The FCU® was developed by Dr. T. Dishion and colleagues in response to decades of research demonstrating how family ecology shapes child mental health risk and resilience (29, 40), and unmet needs for prevention and interventions that effectively engage parents and caregivers living in stressful circumstances. It has been adapted to include families of children from infancy age to young adulthood, and has demonstrated sustained (42), reliable and robust positive effects on multi-informant reports of child, adolescent, and young adult outcomes that are highly relevant to ASD, including direct and indirect effects on: emotional self-regulation (43), disruptive behavior (44), extra-curricular involvement (35) and academic achievement (45), depressive symptoms (46), suicidality (47), family connectedness to service (30), and caregiver mental health (44). The program has demonstrated effective delivery within homes (29), clinics (48), and schools (49).

### Study visit schedule

2.3

See Figure 2. This study will implement two key changes from the FCU® format as typically delivered in clinical settings. First, the order of the first and second FCU® visits will be reversed, so that the assessment is unbiased by whether participating caregivers anticipate receiving the FCU® intervention or not. That is, the multimodal assessment will be delivered at the baseline visit prior to randomization (typically the assessment occurs during the second visit of the FCU®). Second, the baseline assessment will be conducted by research staff rather than FCU® clinicians. These changes are standard in FCU® research (29).

**Figure 2 fig2:**
[figure not shown]
Study flow, effectiveness randomized controlled trial arm. ABC, Aberrant behavior checklist; FCU, Family Check-Up; EDP, Everyday parenting curriculum; SDQ, Strength and difficulties questionnaire.

#### Baseline assessment (3.0 h)

2.3.1

The baseline visit will be conducted in clinic. Families will be engaged in a multi-modal assessment including questionnaires and activities. Caregivers and children (developmental age 11+ years) will complete questionnaires that cover primary, secondary, and exploratory outcomes. Brief child language and IQ tests will be administered. In addition, the family will be asked to do FITs, which will be video-recorded for later coding.

Families randomized to the FCU® arm will be informed that an FCU® clinician will contact them shortly for participation in the FCU®. Families randomized to the TAU arm will be connected to a Family Service Coordinator in the Autism Program, who can direct them to appropriate services that are freely or available as a fee-for-service option. For ethical reasons, families randomized to the TAU arm will have the option to receive the FCU® upon study completion.

#### FCU® visits (FCU® arm only)

2.3.2

All FCU® visits will be conducted by a clinician and will take place in clinic or virtually (dependent on the family’s preference). The Research Coordinator will provide the baseline assessment data, including responses to questionnaires and videos of the family interaction tasks, to the clinician who will then schedule the initial interview with the caregiver.

##### “Get to Know You” initial interview visit (30–45 min)

2.3.2.1

The purpose of this initial visit is to describe the FCU® process, build rapport, and obtain preliminary information about the child and family.

##### Feedback visit (60–90 min)

2.3.2.2

As per the FCU® protocol, the FCU® clinician will engage the caregivers (s) in a feedback session where assessment results are reviewed using a motivational interviewing framework. Youth aged 11 years and older who contribute questionnaire data are invited to receive a separate feedback session with the option of then engaging in a shared feedback session with their parent (s)/caregivers after review of their data and goals. Sensitive caregiver information (e.g., self-reported mental health, parenting) are shared individually with caregivers only and youth choose which aspects of their self-reports they would like to share. The feedback visit concludes with collaborative goal-setting to develop a menu of services that maps explicitly onto family needs. These may include EDP sessions, individual child treatment, connection to parent mental health services, and/or direction to community supports or recreation programs.

##### Everyday Parenting curriculum (60 min—optional)

2.3.2.3

If appropriate, families may access a suite of optional EDP sessions that are tailored in content and number to their feedback. The feedback and EDP sessions (if applicable) must be completed prior to the 6 months assessment.

#### 3-month assessment (30 min)

2.3.3

This is a brief visit that involves an interview and questionnaires to measure primary and secondary outcomes. It can take place in the family’s home, clinic, a community location, or over the phone with questionnaire completion through emailed links.

#### 6-month assessment (1.5–2 h)

2.3.4

The 6-month visit is a repeat of the baseline assessment, with the exception of child IQ and language assessments.

#### 9-month assessment (30 min)

2.3.5

The 9-month visit involves primary and secondary questionnaire outcomes.

#### 12-month assessment (1.5–2 h)

2.3.6

The 12-month visit is a repeat of the 6-month assessment.

#### Post-study visits

2.3.7

According to the health maintenance model, annual “check-ups” help maintain gains, bolster skills, and think ahead to the child’s next developmental period. Therefore, families in the FCU® group will be offered a “booster” FCU® visit that incorporates their 12-month assessment data. Families in the TAU group will connected to an FCU® clinician in order to receive the FCU®.

### Measures

2.4

#### Screening measures

2.4.1

Families will be asked for basic demographic information to determine eligibility (e.g., child date of birth, child’s primary residence and caregivers). To determine if child has a developmental age of at least 2 years, caregivers will be administered item #41 from the Autism Diagnostic Interview (ADI-R) which assesses how well the child uses language to communicate. They will also be asked whether the child can follow simple two-step commands and if they use any alternative communication devices. In addition, caregivers will be asked questions about the presence or absence of intellectual and learning disabilities.

Child EBP will be assessed as follows:

The *Strengths and Difficulties Questionnaire (SDQ)* (45), a widely used 25-item behavioral screening questionnaire for children ages 2–17 years. The Prosocial Behavior scale showcases strengths, while the remaining four evaluate negative behaviors such as emotional symptoms, conduct problems, hyperactivity/inattention, and peer relationship problems. Satisfactory psychometric properties have been reported (45) and scores from the SDQ and the CBCL have been shown to be highly correlated (48). A child is eligible if the conduct score ≥ 4 OR the hyperactivity score is ≥8 OR the emotional problems score is ≥5.

The irritability subscale of the *Aberrant Behavior Checklist (ABC)* (50), a commonly used measure of child EBP in psychosocial and pharmacological RCTs in autism research. Because we aim to recruit children with elevated irritability, participants were included if the ABC irritability score is ≥12 as per norms developed for autistic children and youth (38).

#### Effectiveness measures

2.4.2

##### Primary outcome

2.4.2.1

Child emotional dysregulation will be measured using the Aberrant Behavior Checklist (ABC) Irritability subscale (51) and the Home Situations Questionnaire—Autism Spectrum Disorder (HSQ-ASD; parent report; 0, 3, 6, 9, and 12 months) (52).

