#### Effectiveness

2.1.1

The effectiveness study design is a parallel-group effectiveness randomized controlled trial (RCT) within an Autism Service located within a regional tertiary healthcare center serving a large city and surrounding small-urban and rural areas in Ontario, Canada. A sample of 80 children aged 6–17 years who are functionally speaking (or, “functionally verbal”) with clinically confirmed diagnoses of ASD and high levels of EBP and their families will be enrolled and randomized into either the FCU® or treatment as usual (TAU) with outcome assessments at 0, 3, 6, 9, and 12 months.

We will estimate the effectiveness of participation in the FCU® (+ up to 6 months of optional EDP sessions) vs. Treatment as Usual (TAU) by families of autistic children and youth aged 6–17 years in (a) decreasing child EBP (primary outcome), (b) decreasing caregiver depression, parenting stress, and (c) increasing positive parenting practice. (d) We will describe qualitative and quantitative differences in child and caregiver outcomes and connectedness to child and family services between intervention arms, and between FCU® participants classified as responders vs. non-responders.

Primary and secondary outcomes will be measured at 6 months, with follow-up visits at 9 and 12 months to determine if these effects fade out or are sustained.

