#### Effectiveness—aim #1

2.5.1

Analyses will be conducted following an intent-to-treat approach. Two-wave latent difference score models will be used to evaluate whether participation in the FCU®, compared to TAU, is associated with greater decreases in child EBP (primary outcome) and caregiver depression and parenting stress from baseline to 6 and 12 months post-baseline, and greater increases in positive parenting from baseline to 6 and 12 months post-baseline. A sensitivity power analysis indicates that an *N* = 80 is powered to detect a significant regression coefficient equivalent to Cohen’s *d* = 0.56, α ≤ 0.05 (one-tailed), which is aligned with systematic reviews noting moderate (~*d* = 0.60) effect sizes for parenting programs among caregivers of autistic children (19, 20). A one-tailed test was chosen based on our directional hypotheses and the wealth of evidence supporting the effectiveness of the FCU®. Given that *d* = 0.56 is somewhat larger than that found in previous studies of the FCU® in non-autistic children, we will also conduct two additional sets of analyses. First, we will calculate a Bayes Factor for each analysis to determine whether the pattern of effects are more consistent with the null (the two groups do not differ) or alternative hypotheses (the two groups differ). Second, we will conduct exploratory, descriptive analyses to determine the percentage of participants in each condition defined *a priori* as responders using the ABC and CGI, and describe intervention-, organization and policy-relevant child, family and intervention characteristics in each group.

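### Two unranked primary scales, and an unclear role for 12 months, share a one-tailed 5% level and a detectable effect that fit only one test

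*Protocol article*

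**What the plan says.** **Scales.** Section 2.4.2.1 (Primary outcome) states that the primary construct "will be measured using the Aberrant Behavior Checklist (ABC) Irritability subscale (51) and the Home Situations Questionnaire—Autism Spectrum Disorder". Both are parent-reported, at five time points ("HSQ-ASD; parent report; 0, 3, 6, 9, and 12 months"). Neither scale is placed first, and the section describes no combined score.

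**Timing.** Section 2.1.1 (Effectiveness) sets 6 months for the primary and secondary outcomes, then adds: "with follow-up visits at 9 and 12 months to determine if these effects fade out or are sustained". Section 2.5.1 (Effectiveness, aim #1) instead looks for "greater decreases in child EBP (primary outcome) and caregiver depression and parenting stress from baseline to 6 and 12 months post-baseline", and does not distinguish the two times.

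**Analysis and error level.** Section 2.5.1 specifies: "Two-wave latent difference score models will be used to evaluate whether participation in the FCU®, compared to TAU, is associated with greater decreases". A two-wave model covers baseline and one later visit, so 6 and 12 months are separate models. The same section gives a sensitivity power analysis in which 80 participants can detect one regression coefficient equivalent to d = 0.56, at "α ≤ 0.05 (one-tailed), which is aligned with systematic reviews". It mentions no division of that level. It also promises a Bayes factor for each analysis.

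**Use of the result.** Section 3.6 (Dissemination) makes the next step depend on whether significant intervention effects are shown. Sections 1.3 and 2.1 describe the trial as preliminary and proof-of-principle.

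**The concern.** The outcome and analysis text allows at least two primary comparisons (two scales at 6 months), and four if 12 months is given equal standing. The error level and detectable effect describe one. Two things follow.

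First, the trial has no defined answer if ABC Irritability and HSQ-ASD disagree, or if 6 and 12 months disagree. A reader of the results could not tell whether one significant scale is a positive primary finding.

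Second, whichever success rule is adopted later, one of the two stated figures fails. If either scale is enough, the 5% is not held. If both are required, the power behind d = 0.56 is not held. Because section 3.6 uses significance to decide whether the model is revised and re-evaluated, the success criterion has practical consequences even in a preliminary trial.

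**Working it through.** **Inputs from the protocol article.** N = 80 in two arms; one-tailed alpha 0.05; detectable d = 0.56 (section 2.5.1); two scales (2.4.2.1); 6 months, or 6 and 12 months (2.1.1 and 2.5.1).

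**Assumptions.** 40 per arm, because the article gives no allocation ratio. Power of 80%, because none is stated. A two-group comparison of means in SD units stands in for the latent difference score coefficient. The article gives no correlations between scales or between times, so a range is used.

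**Step 1: reproduce the stated figure.** Detectable d = (z₀.₉₅ + z₀.₈₀) × √(2/40) = (1.645 + 0.842) × 0.2236 = 0.556. The t-based version gives 0.561. Power at d = 0.56 is 80.5% (normal) or 79.9% (t). So d = 0.56 reproduces as one test at the full one-tailed 5%.

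**Step 2: either scale suffices, 6 months only (two tests).** If independent, 1 − 0.95² = 9.75%. With correlation r between the test statistics, the chance is 1 − P(Z₁ < 1.645 and Z₂ < 1.645):

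| r | false-positive chance |
|---|---|
| 0 | 9.75% |
| 0.3 | 9.3% |
| 0.5 | 8.8% |
| 0.7 | 8.0% |
| 0.8 | 7.5% |

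**Step 3: any one of four suffices (two scales, 6 and 12 months).** If independent, 1 − 0.95⁴ = 18.5%. With correlations, the chance is one minus the four-variate normal probability that every statistic is below 1.645. The correlation between different scales at different times is taken as scale correlation × time correlation:

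| scale and time correlation (both) | false-positive chance |
|---|---|
| 0 | 18.5% |
| 0.5 | 15.0% |
| 0.6 | 13.9% |
| 0.7 | 12.6% |
| 0.8 | 11.1% |

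**Step 4: both scales must succeed at 6 months.** With no effect on either scale, the chance that both tests succeed cannot exceed the chance that one does, so it is at most 5%. The cost is power. With a true d = 0.56 on both scales and independent tests, power is 0.80 × 0.80 = 64%. It returns to 80% only if the two tests are perfectly correlated.

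**Step 5: split alpha.** Two-way Bonferroni (one-sided 0.025): d = (1.960 + 0.842) × 0.2236 = 0.63, with 71% power at d = 0.56. Four-way (one-sided 0.0125): d = (2.241 + 0.842) × 0.2236 = 0.69, with 60% power at d = 0.56.

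**Step 6: one scale at 6 months as the only primary test.** Step 1 applies unchanged: 5% and d = 0.56.

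**The case against.** A reader might infer that the plan sets up four primary tests and that the false-positive rate is simply 13-16%. The documents do not support that as a statement of fact. Section 2.1.1 places the primary outcome at 6 months and uses the later visits for "with follow-up visits at 9 and 12 months to determine if these effects fade out or are sustained", and section 2.5.1 never calls 12 months a primary time. The two can be read together, with 6 months testing the effect and 12 months its durability. Four tests follow only from the unranked wording of 2.5.1. The 13-16% range also needs a rule that any one success is enough, which is nowhere stated, and moderate correlations, which the article does not report.

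Three further objections deserve weight.

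- **One construct, one coefficient.** Section 2.4.2.1 names a single construct, 2.5.1 powers a single coefficient, and a latent model could take the two scales as indicators of one factor. That is possible, but the article does not say so. If it is the intention, one sentence would settle the question of scales.
- **Detail left to the full protocol or analysis plan.** A condensed article may leave the success rule there, and its absence alone would not be a finding. What stands is on the page: two scales under the primary heading, two sections that do not match on timing, and an error level and detectable effect that fit one test.
- **Preliminary purpose.** Sections 1.3 and 2.1 lower the standard of error control that one would insist on, and the Bayes factors add another view of the evidence. But 2.5.1 still relies on directional significance tests and 3.6 acts on their result.

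**Conclusion.** The point holds in a limited form. The article names two primary scales without priority and does not carry the 6-month primary time into its analysis section. Its one-tailed 5% and d = 0.56 are correct for a single test only, given 40 per arm and 80% power.

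The size depends on a rule that the article does not state. If either scale suffices, the false-positive chance is about 7.5-10% at 6 months. The range of about 11-18.5% applies only if 12 months is also primary and any one of the four successes counts. Both ranges span assumed correlations from 0.8 to 0. If both scales must succeed, there is no inflation, but power at d = 0.56 is below 80%, and about 64% at independence. Under each of these rules for separately tested scales, one of the plan's two figures needs to change.

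**What to change.** 1. In section 2.5.1, follow section 2.1.1: make baseline to 6 months the primary comparison, and report 12 months as a durability outcome with estimates and confidence intervals.
2. In section 2.4.2.1, name one primary scale and test the other at 6 months only if the first succeeds. This keeps both 5% and d = 0.56. ABC Irritability is the natural candidate because the responder rule in section 2.4.2.2 already uses it, but the choice is for the investigators.
3. Alternatively, keep both scales primary, state the rule (both must succeed, or Holm or Bonferroni), and restate the detectable effect. For a two-way Bonferroni split it is about d = 0.63.

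The cost is wording in two sections and the analysis plan, with no new data, visits or participants. It should be done before outcome data are analysed. There are two downsides. The second scale and the 12-month comparison stop being independent routes to a positive result. Also, under the inclusion criteria in section 2.1.3.1 a child can enter through the SDQ with a low ABC score, and such children have less room to improve on ABC Irritability. That should be weighed when choosing the scale.
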